### Statistical analysis

The statistical package SPSS will be used for analysis. All analyses will be performed according the intention to treat principle.

Baseline characteristics will be described as means and standard deviations. Large differences between treatment groups will be analysed with an independent Student's T-test to verify significance (p-value < 0.05). Significant differences will be adjusted for in the final analysis.

The primary outcome will be analysed using mixed linear models with random effects. The covariates of the random part of the model will be determined using restricted maximum likelihood estimation (REML) and selected on the basis of Akaike Information Criterium (AIC). For the fixed part, models will be constructed containing either the treatment effect adjusted for time with or without an interaction term of these components. The models will be compared using AIC. Missing data will be imputed using multiple imputation.

The estimates of the final model will be used to test whether or not there is a clinical difference between the treatment groups. As described before, the MID is 10 points on the GIQLI scale. Therefore, the MID will be subtracted from the estimated difference between treatment groups and tested with Wald's test against a p-value of 0.10.

Additionally, the 7 point scale reflecting self-reported improvement of complaints over time, will be used to confirm whether the assumption of MID being the equivalent of half a standard deviation, holds.

Categorical outcome measures will tested using the chi-square test (p-value < 0.05) and described as percentages and counts.

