### Sample size

The sample size calculation is based on the minimum important difference* (MID) of the GIQLI score. The MID can be estimated by taking half a standard deviation of a quality of life instrument [7,8].

Based on the studies of Forgione et al and Zdichavsk et al the MID of the GIQLI score is estimated at 10 points [5,6]. They also demonstrated that patients improve with 10 points on the GIQLI score one month to one year after elective resection (111 ± 20.4 and 105.8 ± 15.5) for diverticulitis compared to preoperatively (100 ± 22.1 and 95.3 ± 21.4). In conclusion, a difference of 10 points corresponds with the MID and the expected improvement after elective resection.

To demonstrate this difference using an independent t-test (alpha = 0.05, delta = 10, sigma = 21, power = 0.9) approximately N = 97 patients per group are needed for this study. Therefore a total study population of 194 patients is required to attain statistical significance.

To compensate for a potential loss to follow-up of 10%, 214 patients will be included.

** Minimum important difference (MID): The smallest difference in score in the domain of interest which patients perceive as beneficial and which would mandate, in the absence of troublesome side effects and excessive cost, a change in the patient's (health care) management*.

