#### Randomisation (figure 1)

**Figure 1 F1:**
[figure not shown]
Flowchart DIRECT trial

All patients presenting themselves with persisting abdominal complaints after an episode of diverticulitis and/or a third (or more) diverticulitis recurrence, require to have had a recent radiological examination of the abdomen. Preferably a CT-scan is used. However, ultrasonography may also be used on the condition that bowel wall thickening and abscess size can be assessed accurately. Colonoscopy may be performed on indication to exclude malignancy.

If all inclusion criteria are met, patients are informed about the study protocol by their treating physician. They are given a 3 day reflective period, together with the information package. After the reflective period, the patient is contacted and asked for participation. If the patient decides to take part in the trial, he/she is invited to the local hospital to sign the informed consent. After receiving this consent form, randomisation will be performed centrally by the study coordinator using block randomisation (block size 6) stratified for center and inclusion criteria (persisting abdominal symptoms or frequent recurrences).

Both patients in the conservative and elective resection group will be treated conservatively in case of events during follow-up unless there is an absolute indication for surgery according to the treating physician (e.g. fistula, symptomatic stenosis, perforation with purulent/fecal peritonitis). In addition, in case of persisting abdominal symptoms during follow-up (in the conservative group) which are regarded as unbearable by both patient and treating physician, the treating physician may consult an independent event adjudication committee. The independent committee will advise the treating physician whether or not to abandon conservative management and proceed to elective resection. The final decision is made by the treating physician.

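### Adjustment in the primary model hinges on a significant baseline t-test, so baseline GIQLI would usually not be a covariate, which costs precision and leaves chance imbalance in the result

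*Protocol article*

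**What the plan says.** All of the analysis text is in the Statistical analysis section of the Protocol article. For baseline characteristics it sets a two-step rule. First, "Large differences between treatment groups will be analysed with an independent" Student's t-test at p < 0.05. Then, "Significant differences will be adjusted for in the final analysis". The size at which a difference counts as large is not defined.

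The primary outcome goes into a linear mixed model. Its fixed part is given as treatment and time, and AIC decides whether their interaction is kept. The random part is also chosen by AIC, and its candidate terms are not listed. Neither baseline GIQLI nor a stratification factor is named as a covariate.

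Two other sections bear on this. Data collection says the quality-of-life questionnaires are completed at baseline. Randomisation says allocation is done "using block randomisation (block size 6) stratified for center and inclusion criteria (persisting abdominal symptoms or frequent recurrences".

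**The concern.** A significance test at baseline asks whether the arms differ by more than chance. In a properly randomised trial the answer is known: any difference is chance. The p-value says nothing about whether a variable predicts the outcome, and prediction is what makes adjustment worthwhile. A rule based on that p-value leaves out strong predictors in most trials and makes the primary model's covariate set depend on the data.

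Two things are at stake. One is precision: baseline GIQLI is likely to be the best available predictor of later GIQLI, and leaving it out widens the interval. The other is the reading of the particular trial obtained: an imbalance that just misses significance stays in the treatment estimate. The Sample size section sets the expected benefit equal to the minimum important difference (MID) of 10 points, and the estimate will be judged against that same value. If the planning assumption is right, the estimate will lie near the threshold, where a shift of 2 to 3 points is noticeable.

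The rule suits the stratification factors even less. They are categorical and balanced by design, so a t-test is the wrong tool and would hardly ever bring them in.

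**Working it through.** **Inputs from the Protocol article (Sample size).** The design values are "alpha = 0.05, delta = 10, sigma = 21, power = 0.9"; "approximately N = 97 patients per group are needed for this study"; "To compensate for a potential loss to follow-up of 10%, 214 patients will be included". That gives 214/2 = 107 randomised per arm and 97 per arm after losses.

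**Assumed inputs.** The article gives no baseline to follow-up correlation r, so 0.3, 0.5 and 0.7 are used. It gives no share v of GIQLI variance explained by the strata, so 2% to 20% is used. The formulas take one follow-up time, equal SD at baseline and follow-up, and a common linear slope.

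**1. The plan's own figure.** n = 2(1.960 + 1.282)² × 21²/10² = 92.7, so 93 per arm, or 94 with the exact t distribution (two-sided). The stated 97 is slightly more and gives power 0.910. It is mildly conservative and does not affect this point.

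**2. How often the rule admits baseline GIQLI.** Under randomisation, 5% of the time. It is less often if only differences judged large are tested.

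**3. Imbalance that passes unadjusted.** At 107 per arm, SE of the baseline difference = 21 × √(2/107) = 2.87. Multiplied by t(0.975, 212 df) = 1.971, this gives 5.66 points. At 97 per arm the limit is 5.95.

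**4. Conditional shift.** Without adjustment the expected shift is r × imbalance. At the 5.66-point limit it is 1.70 / 2.83 / 3.96 points for r = 0.3 / 0.5 / 0.7. These are upper limits for imbalances that escape the rule.

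**5. Precision at 97 per arm.** Unadjusted SE = 21 × √(2/97) = 3.02. Adjusted SE = 3.02 × √(1 − r²). If baseline is instead a time-zero response, the treatment-by-time contrast behaves like a change score, with SE = 3.02 × √(2 − 2r).

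| r | Unadjusted SE | Adjusted SE | Unadjusted CI wider by | Change-score SE |
|---|---|---|---|---|
| 0.3 | 3.02 | 2.88 | 5% | 3.57 |
| 0.5 | 3.02 | 2.61 | 15% | 3.02 |
| 0.7 | 3.02 | 2.15 | 40% | 2.34 |

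**6. The rule as a procedure.** It was simulated with 97 per arm, no true effect and 40,000 trials per r. Results for r = 0.3 / 0.5 / 0.7:

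- Mean 95% CI half-width: 5.93 / 5.91 / 5.86 under the rule, against 5.68 / 5.16 / 4.25 with routine adjustment.
- Overall coverage under the rule: 95.3% / 95.7% / 96.3%. Overall type I error: 4.7% / 4.3% / 3.7%.
- About 27% of trials have a non-significant imbalance above one SE. In these the mean shift is 1.2 / 2.1 / 2.9 points and the type I error 5.8% / 7.2% / 9.0%. With adjustment the mean shift is about zero.

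**7. Strata.** Leaving out strata that explain a share v of the variance widens the interval by a factor of about 1/√(1 − v). That is 1.0% at v = 0.02, 2.6% at 0.05, 5.4% at 0.10 and 11.8% at 0.20. Simulated coverage over this range is 95.3% to 97.2%.

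**The case against.** **No bias on average.** Over repeated randomisations the estimate is unbiased, and overall type I error under the rule is at or below 5%. This stands. A reader might infer that the rule biases the trial or inflates its false-positive rate. It does neither overall; the shift is conditional on the imbalance observed, and 2.8 points is the edge of non-significance at r = 0.5, not a typical value.

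**Power.** Baseline adjustment raises the power of a t-test for 10 points at 97 per arm from 91% to 93% / 97% / over 99% for r = 0.3 / 0.5 / 0.7. A reader might credit that gain to the primary test. The article does not support this: those figures belong to the Sample size t-test against zero, whereas the planned Wald test first subtracts the MID. With a true difference of 10 the quantity tested is 10 − 10 = 0, and the rejection rate is about the nominal level whatever the SE. The gain in interval width does carry over.

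**Baseline may be a time-zero response.** The article does not say whether it is. If so, the r × imbalance shift does not apply as stated and the loss at r = 0.7 is smaller (2.34 against 2.15, about 9%). This stands as a limit on size. But at r = 0.3 the change score does worse than no adjustment, and adjustment is more precise at all three correlations.

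**Strata.** A reader might infer that the plan excludes the stratification factors. It does not say so: it says significant differences will be adjusted for, not that nothing else will be, and centre could enter through the AIC-chosen random part. The inclusion criterion, however, has no stated route in. Detail on strata could also sit in a fuller analysis plan that is not shown.

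None of this defends the testing rule, which is stated text and not a gap left for a later document.

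**Conclusion.** The point holds as a matter of precision and pre-specification, not of overall validity. Followed as written, the plan leaves baseline GIQLI out as a covariate in about 95% of possible randomisations. The cost is an interval about 5% / 15% / 40% wider than it need be at r = 0.3 / 0.5 / 0.7, and a conditional shift of at most 2.8 points at r = 0.5.

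That the rule exists and is unsuitable is certain from the text. The size is not: it rests on assumed correlations, a single follow-up time and baseline not being modelled as a response. Several visits or a time-zero response change the size but leave adjustment the more precise choice. For the strata, only the direction is secure: omission makes intervals somewhat conservative, by an amount the article does not allow to be fixed. The change should be made, but the trial does not fail without it.

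**What to change.** In the Statistical analysis section, delete the rule that tests baseline differences and adjusts for significant ones. State instead that the primary mixed model includes baseline GIQLI as a covariate whatever the baseline comparison shows, together with the factors used to stratify randomisation: inclusion criterion, and centre as a fixed or random effect. Baseline characteristics can still be described by arm, without p-values.

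The cost is one paragraph of analysis wording. Every variable is already collected, and neither sample size nor trial conduct changes.

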**Methods/design:**

The DIRECT trial is a multicenter randomised clinical trial. Patients (18-75 years) presenting themselves with persisting abdominal complaints after an episode of diverticulitis and/or three or more recurrences within 2 years will be included and randomised. Patients randomised for conservative treatment are treated according to the current daily practice (antibiotics, analgetics and/or expectant management). Patients randomised for elective resection will undergo an elective resection of the affected colon segment. Preferably, a laparoscopic approach is used.

The primary outcome is health related quality of life measured by the Gastro-intestinal Quality of Life Index, Short-Form 36, EQ-5D and a visual analogue scale for pain quantification. Secondary endpoints are morbidity, mortality and total costs. The total follow-up will be three years.

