### Study endpoints

#### Primary endpoint

Health-related quality of life (HRQoL) objectified primarily by the Gastro-intestinal Quality of life Index (GIQLI) and secondarily by EuroQol-5D (EQ-5D), Short-form 36 (SF-36) and Visual Analogue Score (VAS) for pain. Patients are also asked to point out on a 7 point Likert scale whether their health and complaints have improved or deteriorated in comparison to the previous assessment.

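### AIC decides from the outcome data whether the treatment effect is common or time-varying, and the primary test then uses one difference that the time-varying model does not define

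*Protocol article*

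**What the plan says.** Two steps in the Statistical analysis section of the protocol article matter here.

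- **Candidates and selection.** The fixed part is to come from models "containing either the treatment effect adjusted for time with or without an interaction term of these components. The models will be compared using AIC".
- **Test.** "The estimates of the final model will be used to test whether or not there is a clinical difference between the treatment groups". Specifically, "the MID will be subtracted from the estimated difference between treatment groups and tested with Wald's test against a p-value of 0.10".

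The Primary endpoint section puts GIQLI first ("Health-related quality of life (HRQoL) objectified primarily by the Gastro-intestinal Quality of life Index (GIQLI") and gives no time point. The Secondary endpoints section lists questionnaires at baseline and at 3, 6, 9, 12, 24 and 36 months. The Sample size section uses one independent t-test without naming a visit. Its period of one month to one year describes the cited surgical series.

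**The concern.** Without the interaction, the treatment coefficient is one number, a weighted average of the visit differences. With it, there are six follow-up differences if time is categorical, or a line if time is linear. What the treatment coefficient then means depends on the coding of time; with linear time it is the difference at time zero.

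The final step nevertheless tests one difference minus 10. That is well defined under one candidate model and not under the other, and AIC picks between them after the outcomes are known. The Wald test takes the selected model as given.

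At stake is the meaning of the primary result. One model spans both recovery from surgery and the third year of follow-up, so an effect that changes over time is plausible. In that case early and late visits can lead to different conclusions about the 10-point threshold.

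**Working it through.** **Inputs from the article.** SD 21, difference 10, alpha 0.05 (taken as two-sided), 97 patients per group, six follow-up visits, Wald test at 0.10 (taken as two-sided, critical value ±1.645).

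**Assumptions, not in the article.** Complete data, compound symmetry, within-patient correlation ρ from 0.4 to 0.8, and the waning pattern in step 3.

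**1. The plan's own figure.** The t-test with these inputs needs 94 per group (93 by the normal formula), against about 97 stated. Power at 97 is 0.910, which agrees with the planned 0.9. The standard error (SE) of a difference at one visit is 21 × √(2/97) = 3.02.

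**2. How often AIC keeps an interaction that is not there.** AIC prefers k extra parameters when the likelihood-ratio statistic exceeds 2k.

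| Coding of time | k | Probability |
|---|---|---|
| Linear | 1 | P(χ²₁ > 2) = 0.157 |
| Categorical, 6 follow-up visits | 5 | P(χ²₅ > 10) = 0.075 |
| Categorical, 7 times including baseline | 6 | P(χ²₆ > 12) = 0.062 |

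**3. What is estimated if the effect changes.** Assume true differences of 14, 14, 12, 10, 5 and 2 points at 3, 6, 9, 12, 24 and 36 months. The equal-weight average is 57/6 = 9.5. In simulation AIC keeps the categorical interaction in 98% to 100% of trials. The final model then offers several differences:

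| Difference read | True value | (value − 10)/3.02 | Significantly below 10 | Significantly above 10 |
|---|---|---|---|---|
| 3 months | 14 | 1.33 | 0.1–0.2% | about 38% |
| 12 months | 10 | 0 | 5% | 5% |
| 36 months | 2 | −2.65 | about 84% | 0% |

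For example, at 36 months Φ(2.65 − 1.645) = Φ(1.00) = 0.84. With linear time, the treatment coefficient (time zero) averages 15.4, above every true visit difference.

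**4. Type I error, nominal 0.05 test against zero, no true effect.** If AIC selects (categorical time) and one visit fixed in advance is read whenever the interaction is kept, the rate is about 0.053 to 0.056. If any visit may be read, it is about 0.07 (ρ = 0.8) to 0.096 (ρ = 0.4).

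**5. Power of a fixed contrast, constant 10-point effect, test against zero.** One named visit: about 0.91. The average over six visits has SE 3.02 × √((1 + 5ρ)/6), which is 2.13, 2.46 and 2.75 at ρ = 0.4, 0.6 and 0.8. Its power is 0.997, 0.98 and 0.95.

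**The case against.** The strongest reply is that a condensed article need not name the visit or contrast, and that a full protocol or SAP, not shown, may do so. That stands as far as it goes: the missing visit alone would be no finding. But naming a visit elsewhere would not remove the rule the article does state, under which outcome data choose between two estimands before one unspecified difference is tested. It is also fair that the rule is announced in advance and has only two candidates, so this is not a hidden choice, and that the inflation in step 4 is small.

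Several stronger readings are tempting but not supported:

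- **That the primary instrument is open.** The Abstract is loose ("The primary outcome is health related quality of life measured by the Gastro-intestinal Quality of Life Index, Short-Form 36, EQ-5D"), but the Primary endpoint section ranks the instruments ("objectified primarily by the Gastro-intestinal Quality of life Index (GIQLI) and secondarily by EuroQol-5D (EQ-5D"), and the Sample size and Statistical analysis sections use GIQLI. A family-wise error of 1 − 0.95⁴ = 18.5% over four instruments describes no planned analysis.
- **That power falls to 81%.** If baseline counted as a seventh outcome visit, a constant 10 would average to 10 × 6/7 = 8.57, and the single-visit SE then gives 81%. But a seven-visit average has the smaller SE 3.02 × √((1 + 6ρ)/7), and power is 0.98, 0.94 and 0.88 at ρ = 0.4, 0.6 and 0.8. Nor does the article say that baseline is an outcome visit.
- **That AIC is compared across REML fits with different fixed effects.** The article ties REML to the random part only.
- **That multiple imputation makes AIC selection unworkable.** A rule across imputed data sets can be set, and that is SAP detail.

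**Conclusion.** The point holds as a fault in a stated rule. AIC lets the data determine whether the primary quantity is a common difference or a set of time-dependent ones, and the article's single tested difference has no definition in the second case. The selection rates of 0.062 to 0.157 rest only on the usual chi-square approximation. The contrast between 3 and 36 months rests on an assumed waning effect and shows what can happen; it is not a forecast. The error rates also depend on the assumed correlations. The main harm is a primary result without a fixed meaning. A reader might infer serious type I inflation, but the calculations do not show it.

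**What to change.** Drop AIC selection of the fixed part. State that the primary model is for GIQLI at the post-baseline visits and always contains treatment, categorical time and treatment-by-time. Pre-specify one primary contrast from it: either the difference at one named visit, or an average over named visits with stated weights. Either defines the question; 12 months is one possible visit, not the only valid choice. The other visits become supportive. AIC selection of the random part can stay, because it no longer affects what is estimated.

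The cost is wording, plus a few degrees of freedom if the effect really is constant. A single visit also has somewhat less power (about 0.91) than an average (about 0.95 to 0.997 for ρ from 0.8 to 0.4). Aligning the Abstract with the Primary endpoint section is a minor wording correction that can be made at the same time.

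### The trial is sized to show a 10-point GIQLI difference from zero, but the only test described for the primary outcome is against 10 points at p = 0.10, so the stated 90% power does not apply to it

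*Protocol article*

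**What the plan says.** **Sample size section.** The design calculation is introduced with "To demonstrate this difference using an independent t-test" and uses "alpha = 0.05, delta = 10, sigma = 21, power = 0.9". It concludes that "approximately N = 97 patients per group are needed for this study", 194 in all, raised to 214 for 10% loss to follow-up. The same section states that "a difference of 10 points corresponds with the MID and the expected improvement after elective resection". So 10 points has two roles: it is the smallest difference worth having and also the effect the investigators expect.

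**Statistical analysis section.** GIQLI is analysed with mixed linear models. Then: "The estimates of the final model will be used to test whether or not there is a clinical difference between the treatment groups". The rule follows: "Therefore, the MID will be subtracted from the estimated difference between treatment groups and tested with Wald's test against a p-value of 0.10".

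The section describes no test of the treatment difference in GIQLI against zero. It does not say whether 0.10 is one- or two-sided, or which result counts as showing a clinical difference.

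**The concern.** Subtracting the MID before testing changes the null hypothesis from no difference to a difference of exactly 10 points. Because 10 points is also the expected effect, the effect the trial is planned around lies on the null of the test described. The level also moves from 0.05 to 0.10 without explanation.

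A reader of the sample-size section will believe that the trial has a 90% chance of a positive primary result if resection works as assumed. That holds for a test against zero. It does not hold for showing, with the test described, that the difference exceeds the MID. Since direction and success rule are not stated, a small p-value could mean that the difference is above the MID or below it, and these are opposite conclusions.

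**Working it through.** **Inputs (Sample size section):** difference 10, SD 21, alpha 0.05, power 0.9, 97 per group. **Inputs (Statistical analysis section):** null value 10, level 0.10, sidedness not stated.

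**1. Reproduce the stated power.**
- SE = 21 × √(2/97) = 3.015.
- Power against zero, two-sided 0.05: Φ(10/3.015 − 1.960) = Φ(1.356) = 0.91. The t-test version also gives 0.91.
- Required n per group = 2 × (1.960 + 1.282)² × 21²/10² = 92.7, so 93 (94 with the t distribution), against the stated approximate 97. The gap is small and conservative.
- A one-sided 0.05 would need only 76 per group, so two-sided 0.05 against a null of zero is the reading that fits the design.

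**2. The shifted test at the expected effect.** The test statistic is (estimate − 10)/SE. At a true difference of 10 its expectation is 0, so the chance of rejecting above the MID is the upper-tail level:
- 0.10 two-sided: P(Z > 1.645) = 5%.
- 0.10 one-sided: P(Z > 1.282) = 10%.

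The SE drops out of this result, so more patients, a smaller SD or more visits do not change it.

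**3. What the shifted test needs (SE 3.015).**

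| | 0.10 two-sided | 0.10 one-sided |
|---|---|---|
| Observed difference needed | 10 + 1.645 × 3.015 = 15.0 | 10 + 1.282 × 3.015 = 13.9 |
| True difference for 90% power | 10 + (1.645 + 1.282) × 3.015 = 18.8 | 10 + (1.282 + 1.282) × 3.015 = 17.7 |
| Power at a true difference of 15 | 51% | 65% |

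For comparison, a test against zero at two-sided 0.05 needs an observed difference of 1.960 × 3.015 = 5.9.

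**4. Allowance for repeated measures.** The planned mixed model may be more precise than a t-test at one time point. Assume that the six post-treatment assessments are averaged with a correlation of 0.5, a value the article does not give. The variance factor is (1 + 5 × 0.5)/6 = 0.583, so SE = 3.015 × √0.583 = 2.30. The true difference for 90% power (two-sided 0.10) is then 10 + 2.927 × 2.30 = 16.7. Step 2 is unaffected.

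**5. No treatment effect.** At a true difference of 0, the two-sided shifted test gives p < 0.10 in Φ(10/3.015 − 1.645) = Φ(1.671) = 95% of trials, in each case because the estimate is significantly below 10.

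**The case against.** Four arguments can be made for the plan.

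**The shifted test may only supplement ordinary inference.** The mixed model yields a treatment estimate that can be tested against zero, and the article does not call the MID test primary or decisive. This stands in part: it cannot be said as settled fact that the shifted test decides the trial. But it is the only hypothesis test described for GIQLI, and no test against zero is stated.

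**Success may mean not being significantly below the MID.** On that reading the rule is met in 90 to 95% of trials at a true difference of 10, and a true difference of 0 is usually rejected, so the design separates 0 from 10 well. The text does not say this, however, and failing to reject a difference of 10 does not demonstrate a benefit of that size.

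**Direction and success rule may be in a fuller document.** That is fair for those two details. It does not cover the null value of 10 or the level of 0.10, which the article states and which conflict with its own sample-size section.

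**Stronger readings go too far.** A reader might infer that the trial has only a 5% chance of success at its expected effect. That single figure assumes a two-sided 0.10 and that success means rejecting above the MID, and neither is stated. A reader might also infer that an ineffective operation would be declared beneficial because p falls below 0.10 in 95% of trials. The sign of the shifted estimate shows the direction, and nothing in the article says that such a result would be claimed as benefit.

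**Conclusion.** The point holds as a conflict between two stated rules. The sample size belongs to a test of zero difference at 0.05, and the analysis section describes a test of a 10-point difference at 0.10. The 90% power does not carry over.

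If the shifted test is meant to show a difference above the MID, its chance of doing so at the expected effect is 5 to 10%, depending on sidedness, against about 91% for a test against zero with the same 97 per group. This range needs no assumption about SD, sample size or correlation. The other figures (14 to 15 points observed, 18 to 19 points true for 90% power) rest on the t-test standard error. They fall if the mixed model is more precise, to about 17 points true under the assumed correlation of 0.5 and a two-sided 0.10. The documents do not support a single precise figure for the detectable difference.

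**What to change.** In the Statistical analysis section, make the primary test H0: difference = 0 at two-sided 0.05, matching the sample size. Report the estimated difference with its 95% confidence interval and read it against 10 points:
- lower limit above 10: the difference exceeds the MID;
- interval containing 10: compatible with the MID;
- upper limit below 10: a difference as large as the MID is excluded.

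Keep the shifted Wald test, if wanted, as a secondary test with its direction and level stated. This is a change of wording and alters no patients, visits or data.

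If the shifted test is to stay primary, state its direction and success rule. Say in the Sample size section that the 90% power does not apply at a true difference of 10, and give the detectable difference computed for the mixed model that will be used. Re-sizing instead would be costly. With the t-test formula and a true difference of 15, 90% power needs 2 × (1.645 + 1.282)² × 21²/5², about 303 per group, for a two-sided 0.10, or 232 per group for a one-sided 0.10, against 97 planned.

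Either change should be made before any between-group GIQLI results are seen.
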